### Survey instrument

The survey will be administered online and will be programmed in Oxford University servers with an open source platform. The survey will consist of an initial participant information and consent form, followed by a general welcome, three screening questions, an introduction to the research question and description of attributes (provided in both written and short video formats). For each attribute, respondents will answer warm-up tasks to give their view on the attribute for a hypothetical condition (see online supplemental material 1). This will be followed by the preference elicitations starting with the 10 paired comparisons and then the three kaizen tasks. For both tasks, participants will have the opportunity to complete a practice question. At the end of the elicitation tasks, participants will be asked three debriefing questions covering which exercise they found easier to complete, prefer to complete and easier to understand. Finally, a set of demographic questions will be collected including experience with neonatal/childhood surgical conditions, employment status and education qualifications. For healthcare professionals we will also ask their job title and level of professional experience with neonatal/childhood surgical conditions.

A preliminary mock survey has been completed and is presented in online supplemental material 1. In developing the instrument, preliminary testing was undertaken to maximise user understanding as described in Decision model and descriptive framework.

### Statistical evaluation

#### Data collection, recruitment strategy and sampling

The survey instrument will be completed by (1) a sample of parents of children with a surgical condition, (2) participants who had treatment for a surgical condition as a baby or a child, (3) health professionals caring for those who undergo surgery in childhood and (4) members of the general public. Main data collection will commence in October 2021.

Recruitment materials will be distributed via existing contacts for example, by our PAG, by the project’s ‘experts by experience’, and by the project’s healthcare professional team members; registers and mailing lists of support groups, charities and professional groups/bodies; and open advertising through support groups, charities and professional groups/bodies’ communication channels for example, Twitter, Facebook, e-newsletters and websites. Distribution to health professionals will be via professional bodies. We will also include information on our project website and Twitter account, and advertise via Facebook to share the opportunity as widely as possible. These recruitment strategies have been successfully used in previous quantitative and qualitative studies.^8 10–12 41^

We will use an online panel company to invite adult members of the general public to complete the survey. We will use quotas and a target recruitment strategy to ensure the sample is representative of the UK general population in terms of gender, age, social grade and nation.

In this study, we aim to collect 200 responses from parents and individuals with a surgical condition and 200 responses from healthcare professionals (total of 400) over a 3-month period. We are also aiming to collect 400 responses from members of the general public. This is based on typical sample sizes in the health literature and on simple minimum sample size principles.^42^ Since there are no prior studies, it is not possible to obtain prior values for accurate power calculations. However, we will conduct a pilot study of around 80 individuals to assess whether our choice models will have sufficient power to detect significant differences.

The pilot study will also be used to assess the feasibility of the survey instrument in terms of finding programming errors and the process of data capture. Only participants recruited from the UK will be included in the final analysis.

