#### Data analysis

In the primary analyses, we will estimate a mixed multinomial logit model with individual-clustered standard errors. Unlike the conditional logit, the mixed specification relaxes the assumption of preference homogeneity by allowing individual-specific random parameters.^43^ In the secondary analyses, we will explore preference heterogeneity further by estimating heteroscedastic and latent-class logit models. Although the secondary analysis of preference heterogeneity is more descriptive, we hypothesise that some respondents follow lexicographical processes and that respondents who complete the survey or task more quickly may exhibit greater variance in their responses than respondents who take more time to complete the survey or task. Other behaviours (eg, task sequence, object position) may also be related to stochastic processes.

In the primary analysis, we will test the following hypotheses:

Coefficients are logically consistent and with expected directions.The coefficient for the anchor scenario is negative.Survival and quality of life matter significantly more than the remaining attributes.Survival matters more if child lives in good quality of life and survival matters less if child lives in poor quality of life.Reductions in major planned or emergency operations matter more than reductions in minor or emergency operations.We will observe differences among preferences from the different types of participants but not necessarily between elicitation tasks.

Each type of participant (parents, people who were treated for a surgical condition, healthcare professionals and members of the general public) will have completed the paired comparison and kaizen tasks. Therefore, eight sets of preference data will be available for analysis. We will compare preferences between types of respondent within each elicitation tasks using two approaches. First, latent scale coefficients of the attribute levels will be rescaled using the coefficient for the anchor scenario and predicted choice probabilities for types of respondent compared using mean square and absolute errors. Second, we will examine the relative attribute importance scores by attribute. This involves estimating the range of level combinations for each attribute and applying an attribute-based normalisation to enable comparisons.^44^ A similar approach will be used to compare preference evidence between elicitation tasks.

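### Three recruitment targets but four compared respondent types: parents and treated individuals have no sample size of their own, and the planned comparison measures pick up sampling noise

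*Protocol article*

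**What the plan says.** In the protocol article, Data collection, recruitment strategy and sampling, four groups are to complete the survey. The first two are listed separately: "a sample of parents of children with a surgical condition, (2) participants who had treatment for a surgical condition as a baby or a child". Health professionals and the general public follow.

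The targets are three in number: "we aim to collect 200 responses from parents and individuals with a surgical condition and 200 responses from healthcare professionals", with the sum given as "200 responses from healthcare professionals (total of 400) over a 3-month period", and then "We are also aiming to collect 400 responses from members of the general public". The stated basis is: "This is based on typical sample sizes in the health literature and on simple minimum sample size principles". The section adds that accurate power calculations were not possible without prior values and that a pilot of around 80 people will assess power. The pilot is not described by respondent type. Quotas are mentioned only for the public panel.

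The Data analysis section works with four types: "Each type of participant (parents, people who were treated for a surgical condition, healthcare professionals and members of the general public" is how its count begins, and it concludes: "Therefore, eight sets of preference data will be available for analysis". Types are to be compared within each elicitation task in two ways. One uses mean square and absolute errors between predicted choice probabilities after rescaling by the anchor coefficient. The other uses relative attribute importance scores based on the range of level effects. A difference between participant types is one of the hypotheses listed for the primary analysis, and comparison by participant type is one of the stated Aims.

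**The concern.** The sampling plan and the analysis plan use different groupings. Professionals and the public each have a number behind them. Parents and treated individuals have only a joint number, with no sub-target, minimum or rule for combining them if one is small.

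This matters because of how the types will be compared. An error measure between two sets of predicted probabilities is never negative, and its expected value is above zero even when both groups have the same preferences. It grows as either group shrinks. A range-based importance score is also affected by noise, because the range of noisy estimates tends to overstate the true range. Neither measure comes with a stated interval or reference value. The hypothesis is that differences will be observed, so noise works in its favour. The primary and secondary results then feed the choice of coefficients for the final outcome algorithm.

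**Working it through.** **Inputs.** From the sampling section: targets of 200 (parents and treated individuals together), 200 (professionals) and 400 (public). From Data analysis: four types and two elicitation tasks. From Experimental design: five blocks. From Survey instrument: 10 paired comparisons and 3 kaizen tasks per respondent. The splits of the shared 200 are assumptions, because the document gives none.

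**1. The stated total.** 200 + 200 = 400, which agrees with the article; with the public, 400 + 400 = 800. Reading the sentence as 200 parents plus 200 treated individuals would give 200 + 200 + 200 = 600 before the public, which contradicts the stated 400. The first 200 is therefore shared.

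**2. Sized against analysed.** Analysed: 4 types × 2 tasks = 8 sets. Sized: 3 strata × 2 tasks = 6 sets. The 2 × 2 = 4 sets for parents and treated individuals have no individual size.

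**3. What the shared target allows.** For a group of n: n/5 respondents per block, 10n paired choices, 3n kaizen tasks, and a 95% half-width of 1.96 × √(0.25/n) for a choice share of 50% on a task seen by everyone.

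| Group size n | Per block | Paired choices | Kaizen tasks | Half-width (points) |
|---|---|---|---|---|
| 200 (a sized stratum) | 40 | 2000 | 600 | 6.9 |
| 100 (even split) | 20 | 1000 | 300 | 9.8 |
| 50 (150/50 split) | 10 | 500 | 150 | 13.9 |
| 20 (180/20 split) | 4 | 200 | 60 | 21.9 |

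**4. Effect on the error measure.** Two simulations gave both groups identical preferences. Each used its own set of assumed utilities, a conditional logit and no anchor rescaling. The table shows the mean absolute difference in predicted probability, whose true value is zero. As a hand check, the noise between groups of sizes a and b should scale roughly with √(1/a + 1/b).

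| Split a/b | √(1/a + 1/b) | Ratio to 200/200 | 5.6 × ratio | Simulated, set A | Simulated, set B |
|---|---|---|---|---|---|
| 200/200 | 0.100 | 1.00 | 5.6 | 5.6 | 5.5 |
| 100/100 | 0.141 | 1.41 | 7.9 | 8.0 | 7.7 |
| 150/50 | 0.163 | 1.63 | 9.1 | 9.3 | 9.0 |
| 180/20 | 0.236 | 2.36 | 13.2 | 13.9 | 13.4 |

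The simulated figures follow the scaling closely. On the same scaling, the mean square error grows with the square of the ratio: about 2.0, 2.7 and 5.6 times its value at 200/200.

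Comparisons with the larger groups are also affected. For 20 against 400 public respondents the factor is √(1/20 + 1/400) = 0.229, against √(1/200 + 1/400) = 0.087 for a full stratum of 200, a ratio of about 2.6.

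**5. Effect on the importance score.** In set B the true importance of quality of life was 24.5%; the mean estimate was 22.5% at n = 100, 21.0% at n = 50 and 17.7% at n = 20. In set A the true value was 21.9% and the mean estimate at n = 20 was 17.6%. A small group is thus shifted systematically as well as being more variable.

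**The case against.** The best defence has several parts.

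- **The targets are aims, and the article is open about this.** It says that accurate power calculation was not possible, plans a pilot and names scarce recruitment as a limitation. A condensed article may also leave sub-quotas to a fuller document. This explains why the split is missing. It does not reconcile the two sections, because the article itself fixes both the joint target and the eight-set comparison, and the pilot is not described by type.
- **Separate model fits are not stated.** A reader might infer eight separate mixed logits, each with 22 level coefficients (5 × 3 + 2 + 5). The text speaks of one model and of data sets being available. It also leaves room for linear or quadratic forms, which need fewer coefficients. The point therefore rests on the type-specific comparison, whatever the fitting method.
- **A shortage of treated individuals is not shown.** The parent advisory group is only one channel; support groups, charities, registers, social media and people with lived experience are others. The split is unfixed, but nothing says it will be lopsided.
- **A minimum-size failure cannot be claimed.** A reader might apply the rule of thumb 500c/(ta), with c levels, t tasks and a = 2 alternatives. With c = 6 it gives 500 × 6/(10 × 2) = 150, or 167 with t = 9, so 100 would fall short. With c = 4 it gives 100 or 111. The article does not name its rule or say to which group it was applied, so no such failure follows.
- **A power calculation on single coefficients would miss the target.** The planned comparison uses error measures and importance scores, not tests of level coefficients.

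**Conclusion.** The mismatch stands: three sized strata, four compared types, and four of eight data sets with no size of their own, in a comparison that is both a stated aim and a primary-analysis hypothesis. There is no arithmetic error; the stated total is correct.

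The consequence is imprecision and apparent differences caused by noise. With no true difference, the absolute-error measure is about 5.6 points at 200/200, 8 at 100/100, 9 at 150/50 and 14 at 180/20. These sizes rest on assumed utilities, a conditional logit in place of the planned mixed model, no anchor rescaling, and a stand-in for the actual design, which is in a supplement not shown. Nothing was simulated for the kaizen data. The growth as a group shrinks follows from the scaling in group size and depends little on those choices; the absolute levels do depend on them.

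The documents do not support saying that 100 per group breaks the plan's minimum-size principle, or that treated individuals will be few. The plan should be changed, but the defect does not undermine the study as a whole.

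**What to change.** - Base the primary between-type comparison on the three strata with targets: parents plus treated individuals, professionals, and the public (six data sets). Use a joint model with type interactions that allows for scale differences between types.
- Report parents versus treated individuals as exploratory. Give bootstrap (resampling respondents) or model-based intervals for the error measures and importance scores, so that a difference can be judged against sampling noise.
- State in the sample-size text that the numbers support three groups, and align the eight-set sentence, the between-type hypothesis and the related aim.

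**Cost.** Changes of wording and a modest addition to the analysis, with no extra recruitment. The drawback is that the parent versus treated contrast loses primary status, and the pooled group averages over two kinds of respondent who may differ.

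**If the four-type comparison is essential**, set a minimum for each of the two types within the shared 200, with a pre-stated rule to pool them if one falls below it. Giving each its own 200 would raise the non-public total from 400 to 600 and the overall total from 800 to 1000.

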#### Data analysis

In the primary analyses, we will estimate a mixed multinomial logit model with individual-clustered standard errors. Unlike the conditional logit, the mixed specification relaxes the assumption of preference homogeneity by allowing individual-specific random parameters.^43^ In the secondary analyses, we will explore preference heterogeneity further by estimating heteroscedastic and latent-class logit models. Although the secondary analysis of preference heterogeneity is more descriptive, we hypothesise that some respondents follow lexicographical processes and that respondents who complete the survey or task more quickly may exhibit greater variance in their responses than respondents who take more time to complete the survey or task. Other behaviours (eg, task sequence, object position) may also be related to stochastic processes.

In the primary analysis, we will test the following hypotheses:

Coefficients are logically consistent and with expected directions.The coefficient for the anchor scenario is negative.Survival and quality of life matter significantly more than the remaining attributes.Survival matters more if child lives in good quality of life and survival matters less if child lives in poor quality of life.Reductions in major planned or emergency operations matter more than reductions in minor or emergency operations.We will observe differences among preferences from the different types of participants but not necessarily between elicitation tasks.

Each type of participant (parents, people who were treated for a surgical condition, healthcare professionals and members of the general public) will have completed the paired comparison and kaizen tasks. Therefore, eight sets of preference data will be available for analysis. We will compare preferences between types of respondent within each elicitation tasks using two approaches. First, latent scale coefficients of the attribute levels will be rescaled using the coefficient for the anchor scenario and predicted choice probabilities for types of respondent compared using mean square and absolute errors. Second, we will examine the relative attribute importance scores by attribute. This involves estimating the range of level combinations for each attribute and applying an attribute-based normalisation to enable comparisons.^44^ A similar approach will be used to compare preference evidence between elicitation tasks.

The decision about which coefficients to use in the final algorithm for CSOR will be made by the CSOR Co-investigator Group based on the results of the primary and secondary analyses, feedback from participants and the face validity of the coefficients obtained.

For the final selected model with rescaled coefficients, we will predict the distribution of utilities of all possible combinations of attribute and levels. This distribution will be used to determine the likelihood of a combination to be considered successful or unsuccessful using a traffic light system: green area (high chance to be successful), amber area (uncertainty about success) and red area (not successful). The external validity of this algorithm will be evaluated in a separate study.

This study is expected to be completed by December 2022.

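### Differences between participant types are to be tested, but the described comparison (error between predicted choice probabilities) has no reference distribution and is inflated in the smaller groups

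*Protocol article*

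**What the plan says.** All of this is in the protocol article, mainly under Data analysis.

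- The list of hypotheses opens with "In the primary analysis, we will test the following hypotheses". The sixth reads "We will observe differences among preferences from the different types of participants but not necessarily between elicitation tasks".
- Four participant types each complete two elicitation formats, so "eight sets of preference data will be available for analysis".
- The comparison is introduced by "We will compare preferences between types of respondent within each elicitation tasks using two approaches".
- In the first approach, "latent scale coefficients of the attribute levels will be rescaled using the coefficient for the anchor scenario", with "predicted choice probabilities for types of respondent compared using mean square and absolute errors".
- The second approach is "Second, we will examine the relative attribute importance scores by attribute", after a normalisation by attribute.
- For the two formats, "A similar approach will be used to compare preference evidence between elicitation tasks".

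Under Data collection, recruitment strategy and sampling, the targets are 400 members of the public, 200 healthcare professionals, and 200 for parents and treated individuals together. The split of that last 200 is not given, although the analysis treats them as two types.

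**The concern.** A hypothesis of difference needs a yardstick for how much apparent difference sampling error alone would produce. The two approaches give none. A mean square or mean absolute error between two fitted models cannot be negative and in practice is never zero, so a reader who looks for differences will find them whether or not they exist.

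The yardstick also changes from one pair of types to another, because the targets are unequal. The error expected from chance is largest for parents and treated individuals, the two groups most likely to be small. A ranking of pairs by error would then partly be a ranking by sample size.

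Comparing preferences by participant type is a stated aim of the study. The results are also among the inputs when the co-investigator group chooses the coefficients for the final algorithm.

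**Working it through.** **Plan's own figures.** No significance level, power, effect size or threshold is attached to this comparison, so there is no result to reproduce. The counts agree: 4 types × 2 formats = 8 data sets.

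**Statistic.** For type g, with attribute-level coefficients b_g and anchor coefficient a_g, the predicted probability for pair j is p_gj = 1/(1 + exp(−x_j·b_g/|a_g|)). Over the 45 design pairs, MSE is the mean of (p_1j − p_2j)² and MAE is the mean of |p_1j − p_2j|.

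**Theory.** With identical true preferences and separate samples, the expected squared difference is approximately the sum of the two sampling variances. So E(MSE) ≈ c(1/n₁ + 1/n₂), and MAE grows roughly with the square root of that sum.

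**Simulation inputs from the article:** 45 pairs in 5 blocks, three attributes overlapping in each pair, one anchor task per block, and the levels of Table 2. Dummy coding gives 5×3 + 2 + 5 = 22 coefficients, plus the anchor = 23.

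**Inputs assumed:**
- Coefficients for six operations or infections of −1.0, −0.5, −1.3, −0.7 and −0.8 across the five count attributes, with 0.25 and 0.45 of these for one and two events.
- Quality of life −0.8 (fair) and −2.0 (poor); survival −0.4, −1.2, −1.8, −2.1 and −2.5; anchor −0.8 − 2.5 = −3.3.
- A 100/100 split of the shared 200 (50/150 as a variant).
- Conditional rather than mixed logit, independent choices, and a generated design without the implausibility exclusions.

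**Identical preferences, 600 replicates per row.** Ratios are relative to 200 v 400; the theoretical ratio is √[(1/n₁ + 1/n₂)/0.0075].

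| Pair of types | n₁ v n₂ | 1/n₁ + 1/n₂ | Mean MSE | Mean MAE | Smallest MAE | MAE ratio (theory) |
|---|---|---|---|---|---|---|
| Professionals v public | 200 v 400 | 0.0075 | 0.00050 | 0.0177 | 0.0100 | 1 |
| Parents or treated v public | 100 v 400 | 0.0125 | 0.00084 | 0.0228 | 0.0119 | 1.29 (1.29) |
| Parents or treated v professionals | 100 v 200 | 0.0150 | 0.00104 | 0.0255 | 0.0130 | 1.44 (1.41) |
| Parents v treated | 100 v 100 | 0.0200 | 0.00141 | 0.0295 | 0.0157 | 1.67 (1.63) |
| Same, uneven split | 50 v 150 | 0.0267 | 0.00191 | 0.0341 | 0.0149 | 1.93 (1.89) |

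**A true difference for contrast (400 replicates).** One type was given a 40% larger quality-of-life weight. At 200 v 400 the mean MAE was 0.0262 and the mean MSE 0.00114. Both are below the values for no difference at 100 v 100 (0.0295 and 0.00141), so the measure can rank a real difference below none.

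**Sensitivity (300 replicates).** With all coefficients × 0.6, null MAE was 0.0297 (200 v 400) and 0.0536 (100 v 100), a ratio of 1.80. With × 1.4 it was 0.0132 and 0.0220, a ratio of 1.67.

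**A statistic with a reference distribution.** A pooled-versus-separate likelihood-ratio test on 23 degrees of freedom at 5% rejected in 4.3% (200 v 400), 5.0% (100 v 400), 6.2% (100 v 200) and 5.5% (100 v 100) of runs under identical preferences. It detected the 40% difference in 96% of runs at 200 v 400 and 45% at 100 v 100. When preferences were the same and only response noise differed (coefficients × 0.7 in the group of 200, against 400), this unadjusted test rejected in 70%. A formal test therefore has to leave scale free.

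**The case against.** The strongest reply is that the article never says that the sixth hypothesis will be decided by these errors. It says that hypotheses are tested in the primary analysis, a mixed logit with individual-clustered standard errors, and then describes the comparisons separately. The sampling section expects the pilot to show whether the choice models have power to detect significant differences, which suggests model-based testing. An analysis plan not shown here may name that test. This stands in part: the link is an inference. But no other between-type method is described. The article does not merely omit a detail; it names a statistic that cannot answer the question on its own. The importance scores do not fill the gap, since they are only examined.

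Three stronger readings are tempting and are not supported:

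- *That the comparison mistakes response noise for preference.* If type g's coefficients carry a common scale factor λ, then λb/λa = b/a, so dividing by the type's own anchor coefficient removes it. The normalised importance scores are also free of scale, and heteroscedastic models are planned as secondary analyses.
- *That rescaling distorts the probabilities.* It changes the metric, and towards 0.5 only if the anchor coefficient exceeds 1 in magnitude, which the article does not give. The rescaled values are compared with each other, and no wrong comparison between types has been shown to follow.
- *That these errors determine the final algorithm.* The co-investigator group is to weigh primary and secondary results, participant feedback and face validity.

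The hedged wording about elicitation formats states an expectation compatible with either result. The substantive point there is that the similar approach inherits the same lack of a reference.

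**Conclusion.** The point holds, at moderate severity. As described, the comparison cannot separate a difference in preferences from sampling error, and it makes the smallest groups look most different. Under a 100/100 split, 100 v 100 shows about 1.6 (theory) to 1.7 (simulation) times the error of 200 v 400 with no true difference. A less even split would widen this.

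The absolute errors rest on assumed coefficients, an assumed split and a simplified model, and should not be read as predictions for this study. That the estimate is positive, and larger in smaller groups, follows from the form of the statistic and held in every setting tried. It would be too strong to say that the measure has no null value: in the population it is zero under identical preferences. What is missing is a reference for the estimate.

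**What to change.** 1. Test the sixth hypothesis in one pooled model with participant-type by attribute-level interactions. The null model has common coefficients and a type-specific scale parameter; the alternative has separate coefficients. With 23 coefficients and four types this is 4×23 − (23 + 3) = 66 degrees of freedom. Use a joint test that is robust to clustering by respondent, and state the level.
2. Keep the mean square and absolute errors and the importance scores as descriptive. Show each error beside a permutation reference from shuffling type labels between whole respondents at the actual group sizes, or give respondent-level bootstrap intervals. Shuffling also assumes equal response noise between types, so it supplements the test in step 1 and does not replace it.
3. For the two elicitation formats, resample respondents with both of their task sets together, so that the interval reflects the within-respondent pairing. Do not read a small error as agreement without such an interval.

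The cost is a revised analysis paragraph and modest computing, with no change to data collection. One limit remains: in the simulation the joint test found the 40% difference in only 45% of runs at 100 v 100, so a non-significant result between the small groups should not be reported as similarity.
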